#### Social Validity Scale (SVS; T0 and T1)

The SVS [43] is a questionnaire consisting of 15 questions measured on a 5-point Likert scale to assess the desirability, applicability, clarity, and efficiency of the intervention procedure. In this study, the scale will be used as described by Janssen et al. [44] and Jonker et al. [45]. During baseline assessment, participants answer questions concerning their expectations of the serious game ‘You & I’ at the post-intervention assessment questions concerning their experiences with playing the game.

#### The Reflective Functioning Questionnaire (RFQ; T0, T1 and T2)

The RFQ [48] is a brief self-report screening measure of mentalizing abilities. It consists of eight items measured on a 7-point Likert scale with scores ranging from *strongly disagree* (1) to *strongly agree* (7). The first three items are ‘People’s thoughts are a mystery to me’, ‘I don’t always know why I do what I do’, and ‘When I get angry, I say things without really knowing why I am saying them’. Psychometric properties are good in a normal developing population and in patients with personality disorders. For the purpose of this study, the measure was adapted for adults with intellectual disabilities by removing unnecessary wording and simplifying concepts. The adaptations were made by the first three authors and checked by collaborating researchers with MBID. Moreover, eight experimental items from the RFQ-54 were added to the questionnaire. The instrument was translated into Dutch by the second author. Then, it was translated back to English by the last author. Where necessary, adjustments were made. Any ambiguity was discussed in mail conversation with the developers of the instrument. Therefore, existing psychometric property data did not apply.

#### Radboud Faces Database (RaFD; T0, T1 and T2)

The RaFD [49] is a set of pictures depicting different emotional expressions and is used to assess emotion recognition as a part of mentalization. Participants have to view color photographs of unfamiliar faces portraying 10 different Caucasian and Moroccan adults each displaying five emotions (anger, fear, happiness, sadness, and neutral). A selection of 50 photographs has been made based on the percentage of agreement on emotion categorization, mean intensity, mean clarity, mean genuineness of the emotion, and mean valence of the photograph [49]. The pictures include averted gaze orientations (left and right) as well as direct gaze orientations (frontal). Participants have to indicate for each photograph which one of five emotions the adult depicts. The RaFD has good psychometric qualities in a normal developing population, with an average expression agreement between chosen and targeted emotions of 82% (median 88%, SD = 19%) [49].

#### Perspective Taking (PT) subscale of the Interpersonal Reactivity Index (IRI; T0, T1 and T2)

The IRI [37] is a multidimensional tool measuring interpersonal reactivity. The self-report questionnaire consists of 28 items measured on a 5-point Likert scale with scores ranging from *does not describe me well* (1) to *describes me very well* (5). The measure has four subscales, each made up of seven different items. In this study, only the PT subscale will be used. The PT subscale measures the tendency to take the psychological point of view of others. The first three items are ‘I sometimes find it difficult to see things from the other person’s point of view’, ‘I try to look at everybody’s side of a disagreement before I make a decision’, and ‘I sometimes try to understand my friends better by imagining how things look from their perspective’. The reliability of the subscale is adequate, with Cronbach’s α = 0.73 [50]. A modification of the subscale has previously been used in research on adults with moderate or mild intellectual disabilities, which also indicated adequate reliability for this population with Cronbach’s α = 0.71 [50].

#### Frith–Happé Animations Test (T0, T1 and T2)

The Frith–Happé Animations Test is added because this measure has been previously used with children with intellectual disabilities [51]. It is a nonverbal task to measure mentalizing abilities and therefore is a good addition to the other verbal questionnaires. The Frith–Happé Animations Test [51] consists of a series of computer-presented animations, each lasting 34–45 s. All animations feature one large red and one small blue triangle moving around the screen. There are three types of animations. First, Theory of Mind (ToM) animations in which it is suggested that the triangle anticipates or manipulates the ‘mental state’ of the other. Second, goal-direct action (GD) animations in which the interaction between the triangles can be described in terms of behavioral interaction. Third, random (Rd) animations in which the triangles purposelessly move around without reference to interactions, goals, or intentions.

After each animation, participants were asked ‘What was happening in the animation?’ Verbal descriptions are recorded and scored for complexity of mental state terms used (i.e. intentionality; 0–3) and accuracy of the answer given (i.e. appropriateness; 0–2). Participants are presented with two practice animations (GD and ToM) to ensure they understand the task.

### Stress regulation

The secondary outcome measure of this study is stress regulation.

#### Lifestress Inventory (LI; T0, T1 and T2)

The LI [52] is a 30-item self-report questionnaire which can be used to measure general worry, negative interpersonal interactions, and competency concerns. Participants are first asked to indicate whether they have experienced a stressor. If they do not, participants move on to the next item. If they do, they select one of four answers to indicate the impact of the stressor, ranging from *no stress* (1) to *a great deal of stress* (5). The first three items are ‘Do people treat you as though you are different?’, ‘Have you been getting on with your partner/girlfriend/boyfriend?’, and ‘Have you heard people you know arguing?’ The LI is reliable for administration of people with ID, with Cronbach’s α = 0.85 [52].

#### Perceived self-efficacy scale (stress; T0, T1 and T2)

This is a short nine-item questionnaire which can be used to measure perceived self-efficacy regarding stress regulation. The questionnaire is designed by the researchers of this study using Bandura’s guide for constructing self-efficacy scales [53] and is specifically focused on the skills that have been learned in the serious game ‘You & I’. Self-efficacy is concerned with people’s expectations of executing a particular skill, in this case stress regulation. We expect that if people are aware of actions that have the effect of regulating stress, this will lead to better stress regulation. Participants are asked on a scale from 0 (*not at all sure*) to 10 (*very sure*) how certain they are about how they can know, feel, and cope with stress. The first three items are ‘Feel in my body when I have stress’, ‘Deal with stress well’, and ‘Know that I have stress’.

## Data analysis

All statistical analysis will be conducted using SPSS version 24.0. Descriptive statistics will give insight into the characteristics of the participants. Before analyzing, outliers will be checked and, if necessary, winsorized and partial intention-to-treat analysis will be performed. Demographic variables are used to test for differences in baseline characteristics between the experimental and control groups, and are added as covariates if differences are found. For social validity, average item scores are reported.

Primary and secondary outcome measures of the study (i.e. mentalizing abilities and stress regulation) will be assessed using linear mixed-effects modeling. With Subject at the highest level and Group, Time, and the Group × Time interaction entered as fixed effects, a mixed model fits into SPSS. Furthermore, compliance will be controlled for through anonymous digital game statistics (how often the computer game is completed) and care organization will be the stratifying variable.

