## Hypotheses

The serious game ‘You & I’ is hypothesized to have a positive effect on mentalizing abilities, including the regulation of stress, in adults with MBID. The primary hypothesis is that being randomly assigned to the experimental group that plays the serious game will be associated with an improvement of the mentalizing abilities in adults with MBID as compared to being assigned to a waitlist control group. The secondary hypothesis is that being randomly assigned to the experimental group playing the serious game will be associated with an improvement of stress regulation in adults with MBID.

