### Sample size calculation

Linear mixed effect modeling with two conditions and three repeated measures will be conducted to analyze the effects on mentalizing abilities and stress regulation. The sample size is estimated based on previous studies measuring the mentalizing ability of perspective-taking using the Perspective Taking (PT) subscale of the Interpersonal Reactivity Index (IRI) and stress regulation using the Lifestress Inventory (LI) among people with intellectual disabilities. With the means used from both measures (for means, see [37, 38]), a desired power of 0.90, and α = 0.05, it is estimated that around 144 participants are needed, as calculated in GLIMMPSE [39]. Because there are three assessments, dropout of 20% will be taken into account. Thus, 172 participants will be recruited and randomized into two groups of approximately 86 participants in each group.

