### Study procedure and randomization

Individuals who sign up for the research both via the care organization as well as via the Internet or any other route and who meet the inclusion criteria will receive an information brochure. Persons who want to participate in the study are asked to sign the consent form and return it to the researcher. In case of legal incapacitation, the legal representative of the participant is asked to sign and return a consent form on behalf of the participant.

Data collection for each participant takes 12–14 weeks. Participants will be assessed at baseline (T0), post intervention (T1, 5 weeks after baseline), and follow up (T2, 6–8 weeks after T1). During all three assessments, participants fill out a set of digital questionnaires (for all measurements, see Measures). A software program (e.g. Qualtrics or Survalyzer) will be used to gather data through the digital questionnaires. Completing the questionnaires will take up to 90 min per assessment. During all assessments, an independent researcher is present to assist the participants with completing the questionnaire at home or in their care home. The researchers will follow a standard protocol on how to assist the participants.

After informed consent and baseline assessment, blind for intervention, participants will be individually randomized into two groups using stratified randomization in combination with block randomization with varying block sizes of 4 and 6. To balance contextual factors, randomization will be stratified with regard to care organization. An independent researcher will produce the allocation schedule using a computerized random number generator and afterward conceal the schedule for the researchers. Blinding is only possible for the baseline assessment and, after that, both participants and the researchers will know to which group participants have been assigned.

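### The only analysis population named is a 'partial' intention-to-treat set, although the hypothesis concerns random assignment and the planned model can include everyone randomized

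*Protocol article*

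**What the plan says.** The protocol article, Data analysis, fixes the analysis population in one sentence: "Before analyzing, outliers will be checked and, if necessary, winsorized and partial intention-to-treat analysis will be performed". The article does not explain what 'partial' leaves out and names no other population.

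The Hypotheses section ties the primary hypothesis to allocation: "being randomly assigned to the experimental group that plays the serious game will be associated with an improvement of the mentalizing abilities", compared with assignment to the waitlist.

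The model for the primary and secondary outcomes is a linear mixed-effects model over three assessments: "With Subject at the highest level and Group, Time, and the Group × Time interaction entered as fixed effects". The same section says of game play that "compliance will be controlled for through anonymous digital game statistics (how often the computer game is completed").

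Study procedure and randomization places randomization after consent and the baseline assessment (T0). Both arms are assessed at T0, T1 and T2, and controls may play the game only after T2.

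**The concern.** A hypothesis about being assigned to the game is tested by comparing everyone assigned to it with everyone assigned to the waitlist. Intention-to-treat delivers that comparison, and 'partial' qualifies it away. If participants are removed for reasons that arise after randomization, the groups compared are no longer those that randomization created. If the removed participants would also have changed differently from baseline, the estimated effect is biased. In a superiority trial the awkward case is the removal of people who engaged little with the game and improved less, because that favours the game.

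**Working it through.** **Is a reduced set needed?** Baseline is taken before randomization, so in principle every randomized participant has a T0 score. A linear mixed model takes each participant's available visits and does not require complete cases. Someone with only T0 adds little to the Group × Time contrast, but the model gives no reason to remove that person, and still less to remove someone who has T1 or T2 data. The reduction to 'partial' therefore does not follow from the design or the model.

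**Who could be left out?** The article does not say. Two kinds of rule are possible:
- Levels played: only the experimental arm plays before T2, so this rule can remove people from that arm only.
- Assessments completed: both arms have the same three assessments, so this rule can remove people from either arm.

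**How large could the effect be?** The plan gives no figure for exclusions, so this is an illustration of the one-arm case.

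Inputs from the plan (Sample size calculation): 144 × 1.20 = 172.8, which matches the stated 172; 172/2 = 86 per arm; α = 0.05, taken here as two-sided because the plan does not say.

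Assumptions:
- There is no true effect, and scores are normal with SD 1 at each visit.
- The least engaged 20% of the experimental arm are dropped and all controls kept. Since 0.8 × 86 = 68.8, this gives 69 against 86.
- Engagement correlates r1 = 0.2, 0.3 or 0.4 with the T1 score and r0 with the T0 score.
- The correlation between T0 and T1 is 0.6.

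Steps:
1. Mean engagement of the retained 80%: φ(0.8416)/0.8 = 0.2800/0.8 = 0.350 SD.
2. Bias in the change from T0 to T1: b = (r1 − r0) × 0.350.
3. Standard error of the difference in change: √(2 × (1 − 0.6)) × √(1/86 + 1/69) = 0.894 × 0.1616 = 0.1446.
4. Type I error: 1 − Φ(1.96 − b/0.1446) + Φ(−1.96 − b/0.1446).

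| r1 | r0 = r1 | r0 = r1/2 | r0 = 0 |
|---|---|---|---|
| 0.2 | b = 0; 0.050 | b = 0.035; 0.057 | b = 0.070; 0.077 |
| 0.3 | b = 0; 0.050 | b = 0.052; 0.065 | b = 0.105; 0.112 |
| 0.4 | b = 0; 0.050 | b = 0.070; 0.077 | b = 0.140; 0.162 |

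A simulation of the same scenario (40,000 runs per cell) agrees: about 0.050 in the first column, 0.055 to 0.075 in the second and 0.074 to 0.165 in the third. The check uses the T0–T1 contrast. The T0–T2 contrast follows the same logic with its own correlations.

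**The case against.** The strongest reply is that 'partial' is merely undefined and that a statistical analysis plan, not shown here, may define it. That would hold if the article were silent on the population, but it is not: it commits to something less than intention-to-treat. Any definition that gives 'partial' a meaning departs from a hypothesis framed by assignment.

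Four stronger readings are tempting, and the documents do not support them.

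- *Low players will be dropped.* No exclusion rule is stated. Compliance is to be controlled for, which describes adjustment in the model and not removal of participants. Whether that adjustment is sound is a separate question.
- *Type I error will be 7 to 14%.* Those figures come from comparing arms at one visit: with SE √(1/86 + 1/69) = 0.162 and shifts of 0.070, 0.105 and 0.140 SD, type I error is 0.072, 0.100 and 0.139. The planned model includes baseline among the repeated measures. If engagement relates equally to T0 and T1, the shift cancels from the change. The direction is also assumed: if engagement were related more strongly to T0 than to T1, the bias would run against the game.
- *Unblinded analysts will make these choices.* Study procedure and randomization says: "Blinding is only possible for the baseline assessment and, after that, both participants and the researchers will know to which group participants have been assigned". That concerns the conduct of the study. The article does not say who screens the data or whether group labels are visible at that stage.
- *Winsorizing is itself an error.* The plan says only that "outliers will be checked and, if necessary, winsorized". A rule fixed in advance does not inflate type I error, and the cut-off and trigger are details commonly left to an analysis plan.

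**Conclusion.** The point holds as a fault in the stated analysis population. The article names only a 'partial' intention-to-treat set, does not say whom it omits, and so does not match its own primary hypothesis, although the planned model can include everyone randomized.

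The consequence is conditional. With 20% of the experimental arm excluded on engagement, an engagement–outcome correlation of 0.2 to 0.4 and a T0–T1 correlation of 0.6, two-sided type I error is about 5% if engagement relates equally to T0 and T1, about 6 to 8% if it relates half as strongly to T0, and about 7 to 16% if it is unrelated to T0. None of these assumptions comes from the article, so the range shows what the wording could allow and does not predict what will happen. Exclusion on assessment completion, acting on both arms, was not quantified.

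**What to change.** In Data analysis, replace the partial intention-to-treat wording with text such as: *The primary analysis is by intention-to-treat. It includes all randomized participants in the group to which they were assigned, regardless of levels played, with all available T0, T1 and T2 scores in the mixed model.* Any reduced set, such as completers, should be defined explicitly and reported as a sensitivity analysis.

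Reporting the analysis of unaltered scores beside any winsorized one would be helpful but is optional.

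The cost is wording only: no change in sample size, assessments or model. The change does not remove the need to handle missing T1 and T2 scores, because the mixed model still relies on its missing-data assumption. It does ensure that no randomized participant with usable data is set aside under an undefined rule. If low engagement does go with less improvement, the estimated effect may be slightly smaller than in a reduced set.

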**Methods:**

A two-arm, parallel, superiority randomized controlled trial will be used with 172 adults with mild to borderline intellectual disabilities. Participants will be randomly assigned to either the experimental group to play the serious game ‘You & I’ or a waitlist control group. Participants will be assessed at baseline, post intervention (5 weeks after baseline), and follow-up (6–8 weeks after post intervention). They also will fill in questionnaires for personal factors, personal development, personal well-being, social validity, autism spectrum quotient (demographic variables), mentalizing abilities (primary outcome measure), and stress regulation (secondary outcome measure).

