### Demographic variables

#### Minimal dataset (MDS; T0)

To measure demographic variables, the minimal dataset (MDS) ‘Basic MDS’ and ‘Basic MDS for adults with an intellectual disability’ will be used, including the Personal Wellbeing Index—Intellectual Disability (PWI-ID) [41, 42]. The MDS is a set of questions on demographic variables for everyone who collects data of persons with intellectual disabilities. The MDS focuses on questions in the following domains: personal factors, personal development, and personal well-being. The questionnaire consists of 32 items, measuring, for example, gender, age, and intellectual functioning.

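### Demographic covariates enter the outcome model only if a baseline test finds a difference between the arms, so chance imbalance chooses the model after the data are seen

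*Protocol article*

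**What the plan says.** The Data analysis section sends the demographic variables through a comparison of the two arms: they are "used to test for differences in baseline characteristics between the experimental and control groups, and are added as covariates if differences are found". It gives no test, threshold or list of variables, and names no demographic variable that enters regardless of the result.

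The pool of candidates is wide. The demographic measures include the minimal dataset, of which the article says: "The questionnaire consists of 32 items, measuring, for example, gender, age, and intellectual functioning". The AQ-10 is also filed under demographic variables, in the Abstract and in the Measures section.

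The model itself is described as follows: "With Subject at the highest level and Group, Time, and the Group × Time interaction entered as fixed effects". The outcomes are measured at T0, T1 and T2, and the Sample size calculation section speaks of three repeated measures, so the baseline outcome appears to be in the model as the T0 observation.

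Care organization is handled apart from the demographic variables and without condition: "care organization will be the stratifying variable". This matches the Study procedure and randomization section: "To balance contextual factors, randomization will be stratified with regard to care organization".

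That section also fixes the order of events: "After informed consent and baseline assessment, blind for intervention, participants will be individually randomized into two groups".

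**The concern.** A baseline test in a randomized trial asks whether a difference could have arisen by chance. Under sound randomization after baseline, the answer is known: it did. A small p value says nothing about whether the variable affects mentalizing or stress regulation, and a large one does not make a prognostic variable unimportant.

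Three things follow:

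- A demographic variable that truly predicts the outcome is left out unless it happens to be imbalanced, and an irrelevant one comes in whenever it is.
- The model for the confirmatory analysis cannot be written down before the data are seen.
- The covariate set would differ from one hypothetical repetition of the trial to the next for reasons unrelated to the question.

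This is a rule that the article states, not a detail that it leaves to another document. A separate analysis plan could supply the missing threshold and list, but the model would still depend on the data.

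**Working it through.** The article gives no figure on this point, so there is nothing to reproduce first. The checks ask how often the rule would act by chance, and how much that would matter.

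**1. How often chance adds a covariate.** The 32 items come from the Minimal dataset section. The 5% level per test, the independence of the tests and the number of tests are assumptions. The expected number of false differences is k × 0.05; the chance of at least one is 1 − 0.95^k.

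| Tests k | Expected false differences | Chance of at least one |
|---|---|---|
| 5 | 0.25 | 22.6% |
| 10 | 0.50 | 40.1% |
| 20 | 1.00 | 64.2% |
| 32 | 1.60 | 80.6% |

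Conversely, a given prognostic variable is left out with probability 1 − 0.05 = 95%. With a list fixed in advance, the probability that chance changes the model is 0.

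**2. Effect on error rates and power in a simple comparison.** A simulation took a single endpoint, one covariate, 72 per arm (144 / 2), a two-sided 5% level and 50,000 runs per setting. The effect was (1.960 + 1.282) × √(2/72) = 0.54 SD, which gives about 90% power unadjusted. The covariate–outcome correlations are assumed.

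| Correlation | Type I error, test then adjust | Power, test then adjust | Power, always adjust |
|---|---|---|---|
| 0.3 | about 4.8% | 90.1% | 92.1% |
| 0.5 | about 4.4% | 90.2% | 96.0% |
| 0.7 | about 3.6% | 91.4% | 99.4% |

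Always adjusting held type I error at 5.0%. The stated rule is thus mildly conservative, not anti-conservative. These power gains do not carry over to the planned model, as step 3 shows.

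**3. Effect in the planned mixed model, complete data.** Let y_it = μ_gt + βx_i + person effect + error, with x_i measured once at T0 and entered as a main effect. Each fitted cell mean is μ_gt = ȳ_gt − βx̄_g. The Group × Time contrast at visit t is

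(μ_1t − μ_10) − (μ_0t − μ_00) = (ȳ_1t − ȳ_10) − (ȳ_0t − ȳ_00),

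because βx̄_g cancels within each arm. The covariate therefore cannot move the estimate. A simulation agrees: 172 participants, a random intercept, a strongly prognostic covariate imbalanced by 0.35 SD, 100 runs. The imbalance is one that the rule would catch, since 1.96 × √(2/86) = 0.30 SD. Group × Time estimates changed by less than 1e-14, with a standard error ratio of 1.000.

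**4. The same model with dropout.** With 20% of participants missing some visits (the figure in Sample size calculation), the mean change in the Group × Time estimate was 0.011 to 0.013 against a standard error of about 0.135, that is, 0.011/0.135 = 0.08 to 0.013/0.135 = 0.10 standard errors. The standard error ratio was 0.994 to 0.996, and single p values moved by at most 0.16. A further run gave shifts of 0.07 to 0.12 standard errors. In that run the Group main effect moved by 0.4 to 0.6 standard errors and its standard error fell by about 13%, so the covariate set matters more for a between-arm difference in level than for the interaction.

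**The case against.** The strongest reply is that the rule hardly touches the treatment effect. In a three-visit mixed model with T0 as an outcome, the usual main source of precision, the baseline outcome, is already used, and steps 3 and 4 show that demographic main effects change the interaction not at all or only slightly. This stands, and it sets the size of the finding.

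Some stronger readings are tempting, and the article does not support them:

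- **That the stratification factor can be dropped by the test.** The rule covers demographic variables only. Care organization is named separately and unconditionally. The article does not say in what form it enters the model, but a condensed article may leave that open.
- **That the rule produces false positives or standard errors that are too small.** Type I error in the simple comparison was at or below 5%, and the planned contrast does not move with complete data.
- **That much power is lost.** The gains in step 2 belong to a single-endpoint comparison, which is not the planned analysis.
- **That known prognostic variables are omitted.** The Background links mentalizing to cognitive development, but no correlation with the outcomes is given. The AQ-10 was adapted for this trial and had not been used before in adults with intellectual disabilities.
- **That unblinded analysts choose the model.** Researchers know the allocation after baseline, but the article does not say who analyses.

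It is also fair that 81% is an upper illustration. Nothing says that all 32 items are tested one by one, and items of the embedded well-being index would be correlated. The figure counts how often a covariate enters by chance, not how much harm follows. Even 5 tests, however, leave a chance of about 23%.

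**Conclusion.** The point holds in a limited form. The stated rule selects covariates by chance imbalance and leaves the model for primary and secondary outcomes undetermined until the data are seen. Its likely effect on the Group × Time estimate is nil with complete data and about 0.1 standard error with 20% dropout. The main gain from changing it is to remove a data-driven model choice; the gain in precision is small and arises only with dropout.

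This rests on four assumptions: a 5% level per baseline test; independent tests; covariates entered as main effects without Covariate × Time terms, of which the article mentions none; and the hypothesis being read from the Group × Time term. If the conclusion were drawn from a between-arm difference in level, the choice of covariates would matter more, as step 4 indicates.

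The rule should be fixed before analysis, but it does not put the trial's conclusion at serious risk.

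**What to change.** In the Data analysis section:

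1. Delete the rule that tests demographic variables and adds those that differ.
2. Name a short list of T0 covariates already collected that enter the model whatever the observed balance, for example level of intellectual functioning and age, with the AQ-10 score as an option.
3. State that care organization is in the model as a fixed effect.
4. Present baseline characteristics by arm descriptively, without p values.

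The cost is a change of wording and a few degrees of freedom. No new data are needed and the sample size does not change.

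### Baseline covariates added as main effects leave the Group × Time estimate essentially unadjusted, so the planned correction for imbalance does not reach a covariate that predicts change

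*Protocol article*

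**What the plan says.** The Data analysis section specifies a linear mixed model "With Subject at the highest level and Group, Time, and the Group × Time interaction entered as fixed effects". Group × Time is the only interaction named. Demographic variables are tested for differences between the arms at baseline and "are added as covariates if differences are found". The same section says that "care organization will be the stratifying variable", without giving its form in the model. Under Study procedure and randomization, "randomization will be stratified with regard to care organization".

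The Sample size calculation section describes the analysis this way: "Linear mixed effect modeling with two conditions and three repeated measures will be conducted". There are exactly three assessments, T0, T1 and T2, and every primary and secondary instrument under Measures is scheduled at all three. Three repeated measures must therefore include T0 as an outcome; this is a firm inference, though not stated in those words. The demographic set and the AQ-10 are collected at T0 only, so each takes one value per participant.

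**The concern.** The purpose of adding covariates is to protect the treatment effect from chance baseline imbalance. In this model the treatment effect is the Group × Time term, a difference between arms in change from T0. A covariate with one value per participant and one coefficient shifts a participant's expected score equally at T0, T1 and T2. It is absorbed by the arm difference at T0 and drops out of the change.

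If the covariate acts equally at all visits, the Group × Time effect needed no correction (dropout aside). If it predicts change, a correction is needed and does not take place. The report would then call an effect adjusted for imbalance although the adjustment had hardly touched it. This is separate from how covariates are chosen: a well-chosen, pre-specified covariate entered in this form would be equally ineffective.

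**Working it through.** **Plan's own figures.** The plan gives no figure for the adjustment. Its sample size arithmetic reproduces (144 × 1.20 = 172.8, stated as 172, about 86 per arm) and supplies only the trial size used below.

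**Algebra.** Write the mean of participant i at visit t as m_t + d_t·G_i + b·x_i, with G the arm and x a baseline covariate. Group × Time leaves all six arm-by-visit means free. With complete data and a covariance common to all participants, the fitted arm difference at visit t is

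D_t = (raw arm difference at t) − b̂·(x̄₁ − x̄₀).

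The last term is the same at every visit, so D_t − D_0 equals the raw difference in change whatever b̂ is. With visit-specific coefficients,

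D_t − D_0 = (raw difference in change) − (b̂_t − b̂_0)·(x̄₁ − x̄₀),

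and the adjustment reaches the effect.

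**Check with complete data.** One simulated trial: 86 per arm, three visits, four organizations, residual SD 1, intraclass correlation 0.6, covariate imbalanced by 0.5 SD with slope 0.5, true effect 0.30 at T1 and T2. All of these except the trial size, the visits and the four organizations are assumptions.

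| Model | T0 arm difference | Group × Time T1 / T2 | SE |
|---|---|---|---|
| No covariates | 0.361 | 0.227 / 0.333 | 0.136 |
| Covariate and organization main effects | 0.097 | 0.227 / 0.333 | 0.136 |
| Covariate × Time added | – | 0.195 / 0.348 | 0.142 |

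The main effects lower the arm difference by 0.265 at T0 (0.361 to 0.097 before rounding), at T1 (0.589 to 0.324) and at T2 (0.694 to 0.429). The common shift cancels. Point estimates were also unchanged under unstructured covariance and in a random-intercept REML fit.

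**Standard errors.** These were unchanged under compound symmetry and unstructured covariance. They were not unchanged under every structure: adding the main effect took the T1 SE from 0.2287 to 0.2111 with a diagonal covariance and the T2 SE from 0.1715 to 0.1691 with AR(1). The article names no structure.

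**20% dropout, covariate unrelated to change** (200 simulated trials per scenario):
- Random dropout: mean absolute shift from adding main effects 0.009 (T1) and 0.012 (T2), against SEs of 0.142 and 0.148, so under a tenth of an SE.
- Dropout depending on the covariate alike in both arms: 0.012 and 0.016.
- Dropout depending on the covariate in opposite directions by arm: 0.035 and 0.066. The T2 mean moved from 0.233 to 0.299 (truth 0.30), so main effects removed real bias here.

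**20% dropout, covariate predicting change.** The covariate slope grows by 0.2 per visit; true effect 0.30 / 0.30.

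| Dropout | Unadjusted T1 / T2 | Main effects | Covariate × Time |
|---|---|---|---|
| Random | 0.390 / 0.517 | 0.392 / 0.518 | 0.294 / 0.323 |
| Opposite by arm | 0.344 / 0.287 | 0.390 / 0.373 | 0.313 / 0.298 |

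The expected bias is imbalance × slope on change: 0.5 × 0.2 = 0.10 at T1 and 0.5 × 0.4 = 0.20 at T2. Under random dropout the unadjusted means exceed those of the matching runs without drift (0.290 / 0.316) by 0.10 and 0.20, as they should.

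**Range at a smaller imbalance.** If differences are declared at the 5% level (the article gives no level), the threshold for 86 against 86 is about 1.96 × √(2/86) = 0.30 SD. With an imbalance of 0.31 SD, slopes on change of 0.1, 0.2 and 0.3 give biases of 0.031, 0.062 and 0.093. Sixty simulated trials at slope 0.3 with 20% dropout and no true effect gave 0.097 unadjusted, 0.097 with the main effect and 0.005 with covariate × Time (simulation SE 0.019).

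**The case against.** The strongest reply is that the case rests on silence. The article does not say that covariates enter as main effects only, and the sentence listing the fixed effects leaves out the covariates altogether, so it cannot be the whole specification. A condensed article may leave such syntax to an analysis plan that is not shown. What stands is that main effects are the natural reading and not an explicit exclusion of Time terms. But the article does state a model and an adjustment rule, and together, as written, they do not do what the rule is for.

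A reader might infer that the covariates cannot change the treatment effect at all. The documents do not support that: the plan expects 20% dropout, and with missing visits the estimate moves, usefully so when dropout depends on the covariate. Nor can one say that standard errors are identical under any covariance structure.

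A reader might also infer that stratification by care organization is wasted. The text calls it only the stratifying variable, so a main effect is an assumption. Blocked randomization within organization keeps the arms close to balance on it, and no precision gain from organization × Time has been shown.

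Finally, the bias figures follow from the assumed imbalance and slope. Randomization makes chance imbalance zero on average, so this is error conditional on the imbalance observed. The article identifies no covariate that predicts change. All of this stands and limits the claim about size; it does not affect the cancellation.

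**Conclusion.** The point holds in a limited form and is worth correcting before analysis. If covariates enter as main effects, with T0 among the outcomes and the Group main effect kept as stated, the Group × Time estimate is exactly unchanged with complete data and nearly unchanged (about 0.01 against an SE of about 0.14) under dropout unrelated to the covariate. The adjustment therefore does not correct for an imbalanced covariate that predicts change. Main effects can help where dropout depends on the covariate, and even then they do not remove the bias from differential change. The same applies to care organization only if it enters as a main effect.

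The complete-data cancellation needs no assumed effect size. Every bias figure does: roughly 0.03 to 0.09 SD for a 0.31 SD imbalance with slopes of 0.1 to 0.3, and nothing if the covariate does not predict change.

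**What to change.** In the Data analysis section, state that baseline covariates and care organization enter with their interaction with Time (visit-specific coefficients), alongside Group × Time, and that the T1 and T2 treatment effects come from that model. An alternative that serves the same end is to analyse T1 and T2 as outcomes with the T0 score as a covariate. There, main-effect covariates do adjust the treatment effect; visit-specific coefficients can be kept if a covariate's influence may differ between T1 and T2.

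The cost of the first option is one line of model syntax and plan wording, two extra degrees of freedom per continuous covariate and (4 − 1) × 2 = 6 for four organizations, which is little with 172 participants. The SE may change slightly in either direction: it rose from 0.136 to 0.142 in the complete-data example above and fell from 0.1455 to 0.1447 in another simulated trial. No new data are needed.
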